#### Rate reduction recommendations

Slowing rapid ventricular response is the most common treatment emergency physicians provide their patients with AF and atrial flutter. Intravenous medications, like the non-dihydropyridine calcium channel blocker diltiazem and the beta-adrenergic receptor blocker metoprolol, are effective heart rate-reducing medications (rate reducers) with a rapid onset [72–74]. Unfortunately, bolus doses of intravenous rate reducers can have a relatively short duration of action. The effect of a single bolus of intravenous diltiazem, for example, wanes after 1–3 h. If the rapid ventricular response returns, it can rebound higher than the initial rate. This may prompt another intravenous bolus of rate-reducing medication. If the rapid ventricular response again recurs or persists, a continuous infusion of diltiazem or esmolol may follow, which may result in admission to an observation unit or hospital ward for continued heart rate management.

One strategy to avoid this common route to protracted care is the early administration of oral long-acting rate reducers, e.g., diltiazem XR or metoprolol tartrate. These can be given in addition to (or in lieu of) their intravenous counterparts [29]. The combination of shorter-acting intravenous medications with longer-acting medications has the advantage of providing both immediate and sustained rate-reducing effects. Several studies in different U.S. ED settings have found that treatment pathways encouraging early administration of a long-acting oral rate-reducing medication (with or without a concomitant intravenous rate reducer) decrease hospitalization of stable patients with isolated primary AF [26, 27]. Intravenous magnesium sulfate is another effective rate reducer, which can be helpful independent of a patient’s serum magnesium level [75–77]. Studies have shown continued effect lasting 12–24 h following initial magnesium sulfate administration [75, 77, 78]. Early administration of these “sustainers” (long-acting oral medications or intravenous magnesium sulfate) may reduce the need for hospitalization. We recommend “sustainers” only for normotensive patients with a “good heart,” defined as one with an ejection fraction greater than 50% (based on recent echocardiography or physician gestalt) and no clinical evidence of decompensated heart failure (Fig. 3).

**Fig. 3 Fig3:**
[figure not shown]
The rate control screen in RISTRA-AF for patients with a “good heart”. A good heart is defined as one with an ejection fraction greater than 50% (based on recent echocardiography or physician gestalt) and no clinical evidence of decompensated heart failure. BB, beta-blocker; bpm, beats per minute; CAD, coronary artery disease; CCB, calcium channel blocker; dilt, diltiazem; ED, emergency department; EF, ejection fraction; eGFR, estimated glomerular filtration rate; HBS, hospital-based specialist in internal medicine; HF, heart failure; IV, intravenous; KP, Kaiser Permanente; outpt, outpatient; Pharm, pharmacologic cardioversion; pt, patient; RVR, rapid ventricular response; w/, with

Rate reduction in patients with hypotension, known left ventricular ejection fraction ≤ 50%, or decompensated heart failure is more challenging and warrants a different set of recommendations (Additional file 8). If the physician is intent on attempting electrical cardioversion in the ED and the stable patient is tolerating rapid ventricular response, we recommend against rate-reducing medications, as some evidence suggests they may reduce the effectiveness of electrical cardioversion (Additional file 9) [79]. This does not apply to patients who are to receive oral flecainide or propafenone, as they require a rate-reducing agent to block the atrioventricular node at least 30 min prior to cardioversion [28].

#### Cardioversion

Restoration of sinus rhythm is the most effective means of symptom resolution in patients with intermittent AF and atrial flutter and can be one component of a larger, long-term rhythm control strategy. Among ED patients, elective cardioversion is associated with reduced hospitalization and greater patient satisfaction [42, 80, 81]. RISTRA-AF provides recommendations about which ED patients may be candidates for elective and emergent cardioversion (Additional file 10) [13]. This information is accessible from the module screen via the link labeled “Who” (Fig. 2). Through the link labeled “When” (Fig. 2; Additional file 11), RISTRA-AF reminds physicians of the pros and cons to immediate attempted cardioversion compared with a short-term delay for those with symptomatic AF or atrial flutter of presumed recent-onset (< 48 h). The delayed approach is a “wait and see” approach that involves discharging the patient to home with a scheduled return visit at approximately 40 h post-symptom onset. We leave the timing debate (today vs tomorrow) open to accommodate physician and patient preference as well as varied local practice patterns [82–86]. The link “ED or DC OACs” (ED or discharge oral anticoagulation) summarizes recommendations from varied sources about which patients are thought safe to cardiovert without several weeks of preceding anticoagulation and which patients may benefit from anticoagulation following ED cardioversion (Additional file 12) [12, 13, 28, 87–90].

#### Electrical cardioversion: increasing first-shock success

When physicians elect to pursue ED cardioversion, we provide recommendations in RISTRA-AF to facilitate timely and effective sinus restoration (Fig. 4). With synchronized electrical cardioversion, we recommend maximizing joules to optimize first-shock success and limit sedation time and risk [28, 40, 41]. Most adverse events from electrical cardioversion are associated with sedation and not the procedure itself [91]. We recommend starting with maximal joules, which at present in our EDs is 200 (biphasic). If the first-shock fails, a second shock can be administered at 1 min. We recommend manual pressure augmentation to reduce transthoracic impedance, deliver more current to the heart and increase effectiveness of electrical cardioversion [39, 41, 92, 93]. Manual pressure augmentation has been shown to be safe for the proceduralist [39, 94]. It can be helpful for all patients, but more so for obese patients, who fail electrical cardioversion at twice the rate of non-obese patients [39].

**Fig. 4 Fig4:**
[figure not shown]
Electrical cardioversion screen in RISTRA-AF. AHA, American Heart Association; AL, anterior-lateral; AP, anterior–posterior; BMI, body mass index; DCCV, direct current cardioversion, max, maximize

If the first two shocks with maximal joules and manual pressure augmentation are unsuccessful, a priming dose of ibutilide (1 mg over 10 min) can be used in eligible patients (the criteria are spelled out in RISTRA-AF; cf. Additional file 13), followed by another attempt at electrical cardioversion. This has been shown to increase sinus restoration [28, 95]. In response to failed electrical cardioversion, RISTRA-AF follows U.S. guidelines in suggesting changing pad placement from anterior–posterior to anterior-lateral or vice versa [28]. One can also switch to pharmacologic approaches.

#### Time-efficient pharmacologic cardioversion

Pharmacologic cardioversion is less effective than an electrical approach [42]. However, it may be preferred when patients are poor sedation candidates or refuse electrical cardioversion, if ED nursing staff cannot easily support elective procedural sedation, or if physicians (or departments) prefer a two-step approach, starting with the less resource-intensive pharmacotherapy and reserving sedation and synchronized cardioversion for those who fail step 1 (Fig. 5) [96, 97].

**Fig. 5 Fig5:**
[figure not shown]
Pharmacologic cardioversion screen in RISTRA-AF. A weak heart is defined as one with an ejection fraction less than 50% (based on recent echocardiography or physician gestalt) or clinical evidence of decompensated heart failure. AFIB, atrial fibrillation; AFLUTTER, atrial flutter; AV, atrioventricular; BP, blood pressure; CAD, coronary artery disease; DCCV, direct current cardioversion; IV, intravenous; IVF, intravenous fluid; max, maximum; med, medication; obs, observation unit; pt, patient; pre-labs, pre-treatment laboratory testing; QTc, corrected QT interval; RN, registered nurse; SBP, systolic blood pressure

Our medication recommendations are stratified by rhythm (AF vs atrial flutter), structural heart disease (good vs weak hearts, as defined above), and systolic blood pressure (Fig. 5). For normotensive patients without known structural heart disease, we suggest intravenous procainamide for several reasons: it is easy to administer, has a good safety profile, has a relatively rapid effect (over 50% at 90 m), does not require prolonged monitoring (unlike intravenous ibutilide in all patients [4h], oral flecainide and oral propafenone in drug-naïve patients [8h]), and has been well studied among unselected ED patients with presumed recent-onset AF (< 48 h) [42, 96]. Procainamide is the most common cardioversion medication used in Canadian EDs and the recommended drug-of-choice by the Canadian Association of Emergency Physicians for eligible ED patients with recent-onset AF [3, 12, 98].

Our second-line agents for pharmacologic cardioversion of hemodynamically stable ED patients with AF and good hearts are the oral agents propafenone and flecainide, famously used for the “pill-in-the-pocket” approach to rhythm control [99–102]. Though they may be more effective than procainamide in restoring sinus rhythm, Class Ic agents require pre-treatment with atrioventricular nodal blockers and, on first use, cardiology involvement and at least 8 h of cardiac monitoring, which in our system often involves admission to an observation or inpatient unit. What these medications gain in effectiveness, they lose in efficiency. If effective and safely tolerated in a monitored setting, these oral medications can subsequently be self-administered at home for the treatment of future paroxysmal AF episodes in select patients [100].

For normotensive patients with atrial flutter and no known structural heart disease, ibutilide is our drug-of-choice because of its effectiveness over intravenous procainamide (approximately 62 vs 25% at 90 m) [97, 103]. Intravenous ibutilide administration requires careful patient selection and protocol adherence to reduce the risk of polymorphic ventricular tachycardia, which is rare if ibutilide is properly used (Additional file 13) [97, 104]. The median time to effect of intravenous procainamide and intravenous ibutilide (approximately 30–40 m) contrasts sharply with intravenous amiodarone, which fails to reliably outperform placebo for 6–8 h [43]. This delay is not conducive to timely cardioversion and hampers departmental operational and resource efficiencies, often requiring admission to an observation unit or inpatient ward for administration [12]. Because of its limitations, intravenous amiodarone for ED patients with AF or atrial flutter is reserved for those with hypotension, left ventricular ejection fraction ≤ 50%, or decompensated heart failure, for whom intravenous procainamide and ibutilide, as well as oral flecainide and propafenone, are contraindicated. Because intravenous amiodarone recipients in our model of care are generally higher-risk patients, early cardiology consultation and inpatient monitoring are prudent to personalize safe management.

#### Stroke prevention

One of the most serious complications of AF and atrial flutter is ischemic stroke, which can be significantly disabling, if not fatal. Fortunately, thromboprophylaxis can reduce stroke risk by two-thirds and mortality by 25% [13, 28, 105]. Stroke prevention is a critical component of AF and atrial flutter management in all society guidelines [14, 106]. The ED provides an important opportunity to identify patients who meet criteria for anticoagulation, and ED care may serve as a sentinel moment for behavioral change [46, 107–109]. Initiating stroke prevention therapy at the time of ED discharge to home has been shown to be safe and associated with a mortality reduction [110]. Yet emergency physicians often under-prescribe anticoagulation on discharge of eligible patients with AF and atrial flutter [107, 108, 111]. In some health systems, patients interested in starting anticoagulation who receive a prescription at the time of ED discharge are more likely than their non-treated counterparts to be on anticoagulation one year later [112]. Several ED studies have used clinical decision support tools to increase ED prescribing of oral anticoagulants in eligible AF patients on discharge to home [113, 114].

However, some have debated whether the initiation of anticoagulation at discharge for home-going patients falls within the scope of ED care [115]. What cannot be debated is the value of identifying at-risk patients with AF and atrial flutter and informing them that stroke prevention is an important topic worth exploring with their outpatient physicians. Even a brief discussion on stroke prevention with an emergency physician may move eligible patients one step closer towards anticoagulation.

The CHA_2_DS_2_-VASc score is currently recommended in various society guidelines for stroke risk stratificiation [13, 28]. We opted to use it to identify patients at sufficient stroke risk to warrant anticoagulation, despite its significant shortcomings [116, 117]. To make the CHA_2_DS_2_-VASc score easier to use, we auto-populated it in RISTRA-AF by drawing in comorbidities from the EHR Problem List, as we have done with other clinical applications [17, 60]. All patients in RISTRA-AF receive a CHA_2_DS_2_-VASc calculation unless they have a stroke-prone condition in which anticoagulation is indicated regardless of their risk score: moderate-to-severe mitral stenosis, mechanical valve, or hypertrophic cardiomyopathy (Additional file 7). In these higher-risk patients not currently on anticoagulation, we recommend a consult to the pharmacy-led telephone-based Anticoagulation Management Service.

If the patient has an elevated CHA_2_DS_2_-VASc score (≥ 2 in men and ≥ 3 in women), is not currently taking an anticoagulant, and will be discharged to home, we recommend they receive one or more of the following stroke prevention actions (Additional file 14): (1) a risk-specific educational handout, reviewed at the bedside with the treating physician in a shared decision-making conversation (Additional file 15). The handout is designed to be taken home as part of the patient’s discharge instructions and can be used to facilitate discussion with family and with their outpatient physician; (2) if patients express interest in learning more about the benefits and risks of stroke prevention, the emergency physician can send an electronic consult to the Anticoagulation Management Service, which will contact eligible patients to discuss treatment options; (3) a 30-day prescription of an oral anticoagulant. Currently in our health system, dabigatran is the initially recommended anticoagulant for at-risk patients, if eligible. In RISTRA-AF, we provide guidance on dosing and contraindications (Additional file 14) and link the physician to a patient handout from the health system on the medication. If the physician wants to explore alternative anticoagulants, we provide links to internal resources on how to tailor the anticoagulant choice for patients with AF or atrial flutter.

Some emergency medicine pathways identify patients with AF or atrial flutter who are eligible for anticoagulation by using a high predicted stroke risk combined with a low estimated bleed risk, e.g., the HAS-BLED score [118]. We include on the anticoagulation screen a link to both the HAS-BLED score as well as a summary of how it was designed to be used (Additional files 16 and 17). The fundamental purpose of HAS-BLED is to draw attention to reversible risk factors that need correcting rather than to exclude patients from being recommended anticoagulation if they are at increased risk for ischemic stroke; patients with a higher HAS-BLED score require more careful review and closer monitoring by their outpatient care team [119].

#### Follow-up after ED discharge to home

It is critical to patient care and outcomes that emergency physicians transfer care to outpatient physicians who can continue to manage rhythm-related symptoms via rate or rhythm control and to refer for cardiology management as needed, e.g., for complex cases or procedural intervention like elective outpatient cardioversion or ablation. An equally important component of ongoing primary care management is to proactively manage cardiovascular risk factors and comorbidities such as obesity, hypertension, and diabetes [14, 29, 120, 121]. We recommend that patients with AF or atrial flutter receive timely outpatient follow-up (< 7 days) (Fig. 2). Some multidisciplinary ED treatment pathways for AF and atrial flutter create a new, dedicated outpatient clinic to facilitate post-ED follow-up [114, 122, 123]. Given our integrated health care delivery framework, health plan members have primary care physicians with whom timely follow-up is readily available (and those physicians have access to the same integrated EHR used in our EDs), so the creation of a specific AF clinic for discharged ED patients was unnecessary.

#### Wrap-up and summary

RISTRA-AF provides physicians an efficient way to document a structured summary of their AF-related ED management using the wrap-up screen (Additional file 18). This requires physician input about elements of ED care that we use to build a templated summary paragraph that can be copied from RISTRA-AF for pasting into the ED note of the EHR (Additional file 19).

#### Outcomes

The primary outcome for aim 1 is hospitalization among those with isolated AF or atrial flutter [26, 27]. This includes admission to the inpatient setting and to outpatient observation units. We selected this broad definition to distinguish hospitalization from discharge to home directly from the ED. We will undertake a sensitivity analysis using a stricter definition of hospitalization, which includes only admission to the inpatient setting, to accommodate inter-facility variation in outpatient observation practices. We will also undertake a sensitivity analysis evaluating hospitalization in the larger cohort of patients who were coded as having primary AF or atrial flutter, whether the atrial arrhythmia was isolated or not. This will allow evaluation of possible biases in coding practices and assignment of isolated status.

Secondary outcomes for aim 1 include (a) discharge to home < 24 h of ED registration; (b) total length of stay in the ED and hospital; and (c) ED administration of a long-acting rate-reducing medication among patients who received any rate-reducing medication, oral or intravenous, short- or long-acting. Long-acting rate-reducing medications include oral diltiazem XR, metoprolol tartrate, metoprolol succinate, and atenolol and intravenous magnesium sulfate, 2 g or more. We will undertake a sensitivity analysis in which only 4 g or more of intravenous magnesium sulfate will count as a long-acting rate-reducing medication, as recommended in RISTRA-AF. We are not including amiodarone among our rate-reducing medications because amiodarone can also be used for cardioversion, and we cannot readily distinguish the two indications. Another secondary outcome for aim 1 is administration of continuous IV infusion of diltiazem or esmolol, which may be reduced in patients receiving early long-acting rate-reducing medications.

The primary outcome for aim 2 is anticoagulation initiation in eligible patients with AF or atrial flutter at the time of ED discharge to home or within the following 30 days. Eligibility includes an elevated CHA_2_DS_2_-VASc score (≥ 2 in men and ≥ 3 in women) in health plan members not currently taking anticoagulants who are being discharged to home directly from the ED. Current anticoagulation use is defined using EHR data. A patient is considered to be taking oral anticoagulation if (a) any oral anticoagulation prescription was filled in 45 days prior to the index encounter, (b) the supply of a filled prescription would include the index encounter date, or (c) active use of an oral anticoagulant was documented in the medication review during the index encounter or during the 30 days prior. A secondary outcome of aim 2 is electronic consultation of the Anticoagulant Management Service, independent of anticoagulation initiation in eligible patients (defined above).

We will measure use of RISTRA-AF but have not made it a major outcome. Use of the tool may not correlate strongly with use of the management principles that the decision support tool recommends [124]. For example, a physician may use RISTRA-AF to learn that the most effective means of electrically cardioverting an obese patient involves starting with maximal joules combined with manual pressure augmentation. This management principle is easily remembered and may be employed in future cases without recourse to RISTRA-AF. Frequency of tool use would serve as a poor indicator of frequency of optimal electrical cardioversion technique. We observed a similar pattern in prior decision support research on site-of-care decision-making for ED patients with acute pulmonary embolism. Over the course of the 4 years following the initial implementation of the decision support tool, the frequency of safe outpatient management of ED patients with low-risk pulmonary embolism increased though tool use decreased [54]. These two cases (electrical cardioversion of AF and outpatient management of low-risk pulmonary embolism) illustrate why use of our RISTRA tools is optional. We provide these tools to aid clinicians with management decisions if they feel assistance is needed. Use of the CDSS is not mandatory.

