**1. Sustained rate reduction**	
Administer long-acting rate-reducing medications early in the ED encounter, either in addition to or in lieu of standard intravenous bolus medications	Medications with sustained effect on rapid ventricular response have been central to multifaceted ED interventions associated with reduced hospitalization of patients with isolated AF or atrial flutter [26, 27].

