Given the many variables we are collecting during this trial, we also will be able to address other important clinical questions. For example: What is the association of short-acting oral rate-reduction medications (e.g., diltiazem 30 mg) with hospitalization? Is timing of administration of long-acting rate-reducing medications (e.g., early vs late in the ED course) associated with ED length of stay and hospitalization? How does hospitalization prevalence compare between those receiving different doses of intravenous magnesium sulfate? What are the prevalence and effects of administering both non-dihydropyridine calcium channel blockers and beta-blockers? Was the trial intervention associated with a change in cardioversion prevalence and success and in selection of cardioversion agents (e.g., electrical vs pharmacologic; procainamide vs ibutilide) for AF and atrial flutter? What is the association of stroke prevention actions in the ED with the short- and long-term incidence of ischemic stroke and death among patients eligible for anticoagulation on ED discharge to home? Was the trial intervention associated with other measures of patient care recommended by RISTRA-AF, e.g., ordering of thyroid-stimulating hormone and echocardiography testing when indicated?

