The O’CAFÉ trial differs in several ways. We included a broader population of patients with AF and atrial flutter; we did not limit eligibility by hemodynamic stability or arrhythmia duration, for we sought to address care for a wide spectrum of patients with primary AF and atrial flutter. Our strategy of recommendations was also different. Unlike the RAFF-3 trial, we did not seek to increase cardioversion and decrease rate control strategies, even for patients with presumed recent-onset AF or atrial flutter. We let the treating physician decide whether rhythm or rate control was indicated, only reminding them of when different strategies might be appropriate. Our rate and rhythm recommendations focused on ways of optimizing the chosen intervention. For the physician pursuing cardioversion, for example, we recommend methods to increase first-shock success. For the physician pursuing rate reduction, we recommend long-acting medications that facilitate sustained rate reduction and have been associated with reduced hospitalization.

Other ED-based trials have addressed more specific questions of AF management among subpopulations of ED AF patients, e.g., rapidity of rate reduction (intravenous diltiazem vs intravenous metoprolol) [72, 73], method of cardioversion (pharmacologic vs electrical) [129, 130], medication of cardioversion (e.g., intravenous vernakalant vs intravenous ibutilide) [131], timing of cardioversion (early vs delayed) [82, 83], and location of acute management (observation unit vs inpatient ward) [132].

Our decision support application did not have only treating physicians in view. We were equally mindful of our patients. Reducing hospitalization, one of our study aims, is an outcome valued by patients [133, 134]. Symptom reduction is also highly prized by patients. We pursued this patient-centered outcome by seeking to improve sustained rate reduction and increase the success of cardioversion, both of which reduce symptoms caused by the rapid ventricular response common in patients with AF and atrial flutter.

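### The long-acting rate-reducer outcome uses a denominator formed after exposure to the intervention, so it can move in either direction with no change in long-acting use among all patients

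*Protocol article*

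**What the plan says.** The Outcomes section of the protocol article defines Aim 1 secondary outcome (c) as "ED administration of a long-acting rate-reducing medication among patients who received any rate-reducing medication, oral or intravenous, short- or long-acting". The one sensitivity analysis stated for it concerns the magnesium threshold: "We will undertake a sensitivity analysis in which only 4 g or more of intravenous magnesium sulfate will count as a long-acting rate-reducing medication". That leaves the restriction to treated patients in place. No version with all eligible patients as the denominator is stated, and no expected rate or power is given for this outcome.

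The tool's content bears on both parts of the fraction:

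- **Numerator.** Table 1, item 1: "Administer long-acting rate-reducing medications early in the ED encounter, either in addition to or in lieu of standard intravenous bolus medications".
- **Denominator, withholding.** Under Rate reduction recommendations, for a stable patient who tolerates the rapid rate and whose physician intends electrical cardioversion: "we recommend against rate-reducing medications, as some evidence suggests they may reduce the effectiveness of electrical cardioversion".
- **Denominator, adding.** In the same place, on recipients of oral flecainide or propafenone: "they require a rate-reducing agent to block the atrioventricular node at least 30 min prior to cardioversion".

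Analytics and sample size says that every analysis follows intention to treat and uses mixed models with adjustment for time.

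**The concern.** Randomization of clusters to crossover times makes control and intervention patients comparable, after adjustment for time, when the analysed group is fixed before treatment. Here the group is fixed by a treatment decision, and in the intervention condition the tool gives advice on that decision. Patients in the denominator before and after crossover may therefore be differently selected, even though every site is analysed by its assigned condition.

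The consequence is one of interpretation. Sustained rate reduction is one of the routes by which the article expects hospitalization to fall, and outcome (c) is the listed outcome that measures uptake of long-acting agents. A rise could come from more long-acting use, from fewer patients receiving only short-acting agents, or from both. A flat result could hide a real gain. The proportion alone does not separate these.

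**Working it through.** The article gives no figure for this outcome, so there is nothing to reproduce. The check asks how far the defined proportion can move when long-acting use among all patients stays the same.

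**Inputs.** All frequencies are assumptions, because the article gives none. Per patient in the whole eligible group:

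- D = share given any rate reducer under control (0.60 to 0.80)
- L = share given a long-acting one (0.15 or 0.30)
- s = share who would have had only a short-acting agent and now receive no rate reducer (0.05 to 0.15)

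**Formulas.** Control: L/D. Intervention: L/(D − s). All-patient proportion: L in both conditions, so its change is 0.

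**Simple case, per 100 patients.** Under control 60 are treated and 24 of them receive a long-acting agent: 24/60 = 40%. If 10 who would have had only a short-acting agent now have none: 24/(60 − 10) = 24/50 = 48%. Over all patients it is 24/100 in both conditions.

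**Over the range.**

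| D | L | s | Control | Intervention | Apparent change (points) | All-patient change |
|---|---|---|---|---|---|---|
| 0.80 | 0.15 | 0.05 | 18.75% | 20.0% | +1.3 | 0 |
| 0.80 | 0.15 | 0.15 | 18.75% | 23.1% | +4.3 | 0 |
| 0.70 | 0.30 | 0.10 | 42.9% | 50.0% | +7.1 | 0 |
| 0.60 | 0.30 | 0.05 | 50.0% | 54.5% | +4.5 | 0 |
| 0.60 | 0.30 | 0.15 | 50.0% | 66.7% | +16.7 | 0 |

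The first and last rows are the extremes of the 18 combinations examined.

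**Opposite direction.** If a further 0.05 of patients receive only a short-acting agent as pre-treatment, with D = 0.70 and L = 0.30, the proportion falls from 0.30/0.70 = 42.9% to 0.30/0.75 = 40.0%, again with L unchanged.

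**A real gain is also misstated.** If 0.05 of patients, previously untreated, newly receive a long-acting agent, the true gain is 5.0 points. The defined proportion becomes (L + 0.05)/(D + 0.05). At D = 0.80, L = 0.30 it moves from 37.5% to 0.35/0.85 = 41.2% (+3.7). At D = 0.60, L = 0.15 it moves from 25.0% to 0.20/0.65 = 30.8% (+5.8).

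**Chance of a nominal finding.** Take the article's expected isolated counts for the roll-out (567 usual care, 460 intervention) and the middle case. The groups compared are 567 × 0.70 = 397 and 460 × 0.60 = 276. A two-sided 5% test (an assumed level) would be significant about 45% of the time with L unchanged. Over the 18 combinations the figure runs from 6.5% to 97%. It treats patients as independent and ignores time effects, so it is only a rough guide.

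**The case against.** The best defence is that the conditional proportion is the right measure of what the tool teaches. The Discussion presents the advice as optimizing whichever strategy the physician has chosen, so the choice of agent once rate reduction is under way is a proper target. It also says that "we did not seek to increase cardioversion and decrease rate control strategies, even for patients with presumed recent-onset AF or atrial flutter". The advice to withhold applies only where electrical cardioversion is already intended in a stable patient. Tool use is optional. Flecainide and propafenone are second-line, and the pre-treatment statement is an exception to the advice to withhold, not a new push. An all-patient denominator has its own weakness: it counts as non-recipients patients who needed no rate control and patients for whom the tool does not recommend a long-acting agent.

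Much of this stands. The stated proportion deserves to be kept, and the shift may be small. But the stated intent does not remove the problem. The advice to withhold can shrink the denominator even if cardioversion is no more frequent, because it concerns patients who would be cardioverted anyway. The article itself leaves open whether frequency changes: "Was the trial intervention associated with a change in cardioversion prevalence and success" is listed among the further questions to be studied.

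Timing also matters. Protocol version 10 is dated February 2023, enrollment was to end in April 2023, and site feedback on long-acting use began in June 2022. Demoting the stated outcome now would be a late change made after such data had circulated. That argues for adding measures and against replacing the outcome.

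**Conclusion.** The point holds as a caution about one secondary process outcome. Its denominator is formed after exposure, the tool's advice bears on who enters it, and the only stated sensitivity analysis keeps it. Under the assumed inputs, withholding short-acting agents alone produces apparent rises of 1.3 to 16.7 points with all-patient long-acting use unchanged, and added short-acting pre-treatment pushes the other way. The true size and direction cannot be derived from the article.

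A reader might infer more than the document supports:

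- **That the tool demonstrably changes the denominator, or that any observed rise would be an artefact.** The article shows advice bearing on membership; it reports no frequencies and no observed shift.
- **That randomization is lost for this outcome.** The supportable statement is that the comparison may be biased.
- **That this is the main evidence on mechanism.** It is one of several secondary outcomes. Continuous diltiazem or esmolol infusion also bears on mechanism and is stated without this restriction.
- **That magnesium raises the indication problem for which amiodarone was left out.** The article describes magnesium only as a sustained rate reducer, so a patient given it is one whom the outcome is meant to count. Nor is pre-treatment before flecainide or propafenone a close parallel to amiodarone, since the article itself calls that drug a rate-reducing agent.

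The primary hospitalization outcome is not conditioned on treatment and is not affected.

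**What to change.** Keep outcome (c) as defined and describe it as the choice of agent among treated patients. Add two measures, by condition and with the same mixed model:

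1. the proportion given a long-acting agent among all eligible Aim 1 patients;
2. the proportion given any rate reducer in the same group.

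State that the report will claim increased long-acting use only if measure 1 supports it, and will use measure 2 to interpret any movement in outcome (c). If the analysis plan does not already contain these measures, record them as additions with a date.

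The cost is small. Data collection and management says that long-acting administration is available on all study patients regardless of health plan membership, and receipt of any rate reducer must already be derived to form the present denominator. No new data are needed, only wording and two more model fits. The downside is a lower headline percentage and some dilution in measure 1 from patients who needed no rate control.
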